#### Sample selection

The sample will be obtained from the subjects remained in the study to the assessment in 2006. Random sampling stratified by groups A, B and C will be performed to obtain a proportional size of subjects in each group for the purpose of obtaining a balanced sample.

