### Subjects

#### Study population

Subjects will be selected from the PEPAF project cohort[39,40]. This is a cohort composed of 5,451 subjects identified at the start of the study and divided into three physical activity exposure levels: A) 1,163 sedentary in 2003, who became active in 2006, B) 1,942 who remained sedentary during the 24 months of follow-up, and C) 2,346 who were active at baseline assessment. The study will include subjects aged 20-80 years who agree to participate in this study and sign the informed consent. The exclusion criteria were: known coronary or cerebrovascular atherosclerotic disease, heart failure, moderate or severe COPD, walking-limiting musculoskeletal disease, advanced respiratory, renal or hepatic disease, severe mental diseases, treated oncological disease diagnosed in the past 5 years, pregnant women and terminal patients.

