#### Sample size

Sample size was estimated using AIx as a indicator of central arterial stiffness. The CAFE study[15] (ASCOT sub-study[14]) found a difference between the two groups of 6.5 (5.8-7.3) percentage points and this was associated with a difference in cardiovascular morbidity and mortality. The aim is to obtain a size sample sufficient to detect a difference of 3 percentage points of AIx between sedentary, sedentary who became active, and active subjects. There are therefore 3 study groups, assuming a standard deviation of 11, with an alpha risk of 0.05 and a beta risk of 0.20 in a two-sided test, assuming a no response rate of 20%, 352 subjects are required in each group, or a total of 1,056 subjects, but considering a proportional sample to the reference population 1,499 subjects are required. As there will be six participating groups, the sample will be 250 subjects per group for a total of 1,500 subjects, distributed in Groups A, B and C.

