### Methodological limitations

The main limitation in the first phase of the study is that it is a cross-sectional design and therefore only allows detection of association and not causal relationship. This problem is expected to be solved in the second phase with randomized clinical trial that is planned. Selection of the sample was randomized and so it would ideally represent the population without cardiovascular disease seen in primary care, but the losses suffered by the cohort during follow-up were close to 20% and this may have influenced the representativeness of the population attending primary care centers.

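### The sampling rule calls for a sample that is both proportional and balanced, which the stated strata do not allow, and the stated total of 1,499 does not follow from 352 per group on those counts

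*Protocol article*

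**What the plan says.** The Study population section describes a cohort of 5,451 in three strata. It lists the first two as "A) 1,163 sedentary in 2003, who became active in 2006, B) 1,942 who remained sedentary during the 24 months of follow-up". The third stratum, C, is the remaining 2,346, already active when the cohort was first assessed.

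The Sample size section aims to "detect a difference of 3 percentage points of AIx between sedentary, sedentary who became active, and active subjects", "assuming a standard deviation of 11, with an alpha risk of 0.05 and a beta risk of 0.20 in a two-sided test", and "assuming a no response rate of 20" percent. It concludes that each of the three activity groups needs 352 subjects (1,056 in all). It then says that, "considering a proportional sample to the reference population 1,499 subjects are required", and rounds this to 1,500, recruited as 250 at each of six research groups. It gives no target for A, B or C separately.

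The Sample selection section takes the sample from subjects still in the study in 2006, stratified by A, B and C, "to obtain a proportional size of subjects in each group for the purpose of obtaining a balanced sample". The Methodological limitations section adds that "the losses suffered by the cohort during follow-up were close to 20" percent.

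**The concern.** Proportional and balanced allocation are different designs when the strata differ in size, and here the largest is about twice the smallest. With no A, B and C targets anywhere in the article, one centre could sample in proportion and another equally, and both could claim to follow the rule.

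The sample-size paragraph has a related gap. It moves from 352 per group to 1,499 in total without showing the step. A reader cannot tell whether 352 is meant to hold in every group or applies only to equal groups, nor which significance level lies behind either figure. At stake are whether the stated sample size can be reproduced, which sampling fractions are used, and what power each contrast can be said to have. The contrasts involving group A, the smallest stratum, are the most affected.

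**Working it through.** **Inputs.** From the Sample size section: difference 3 points, SD 11, two-sided alpha 0.05, power 80%, non-response 20%. From the Study population section: A 1,163, B 1,942, C 2,346, total 5,451.

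**1. Reproducing 352.** For two equal groups, n = 2 × [11 × (z_alpha + 0.8416)/3]², then divided by 0.8 for non-response.

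| Two-sided alpha | z_alpha | n evaluable | n / 0.8 |
|---|---|---|---|
| 0.05 (stated) | 1.960 | 211.0 | 263.8 (265 if n is first rounded up to 212) |
| 0.05/2 | 2.241 | 255.6 | 319.5 (320 if n is first rounded up to 256) |
| 0.05/3 | 2.394 | 281.5 | 351.9 |

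The stated alpha does not give 352. Dividing it by three, for the three pairwise comparisons, does. A one-way ANOVA F test with means spread over 3 points needs 261 per group, or about 327 after inflation, which does not match either.

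**2. What proportional sampling gives.** The shares are 1,163/5,451 = 21.3%, 1,942/5,451 = 35.6% and 2,346/5,451 = 43.0%. Applied to 1,500, they give 320, 534 and 646. An equal split would be 500, 500 and 500.

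**3. Does 1,499 follow from 352?** On the stated counts there are two natural routes:
- Keep 352 in the smallest group: 352 × 5,451/1,163 = 1,650 (352, 588 and 710).
- Size A v B, the tightest pair, with unequal groups at the alpha that reproduces 352: (352/2) × (1/0.2134 + 1/0.3563) ≈ 1,319, of which about 281 are in A.

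Neither gives 1,499.

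**4. Where 1,499 could come from.** Two reconstructions fit, and the article states neither:
- Alpha 0.05/2: 256/0.8 = 320 in A, and 320 × 5,451/1,163 = 1,499.8.
- 352 kept in A with a smaller 2006 frame. If C alone lost 21.2% (an assumption), the frame is 1,163 + 1,942 + 1,849 = 4,954, A's share is 23.5%, and 352 × 4,954/1,163 ≈ 1,499. A 20% loss in C alone gives about 1,508.

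The frame matters. If losses were the same fraction in every stratum, 1,650 is unchanged. If 20% of the whole cohort was lost and none of it from A, the frame is 0.8 × 5,451 ≈ 4,361 and 352 in A needs 352 × 4,361/1,163 ≈ 1,320.

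**5. Power with 1,500 sampled and 80% response.** SE = 11 × √(1/n₁ + 1/n₂), and power = Φ(3/SE − z_alpha). Evaluable numbers are 256, 427 and 517 under proportional sampling, and 400 in each group under equal sampling.

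| Contrast | SE, proportional | Power at 0.05 | Power at 0.05/3 | SE, equal | Power at 0.05, equal | Power at 0.05/3, equal |
|---|---|---|---|---|---|---|
| A v B | 0.869 | 93.2% | 85.5% | 0.778 | 97.1% | 92.8% |
| A v C | 0.841 | 94.6% | 88.0% | 0.778 | 97.1% | 92.8% |
| B v C | 0.719 | 98.7% | 96.2% | 0.778 | 97.1% | 92.8% |

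**The case against.** A reader might infer that group A, at 320 against 352, is too small. That does not follow. The 352 belongs to the equal-allocation calculation, and the text then turns to a proportional sample. With unequal groups the smallest one needs fewer, about 281 in the A v B calculation, because the larger partner compensates. Proportional sampling of 1,500 also beats the plan's equal 1,056 on every contrast: SE 0.869, 0.841 and 0.719 against 11 × √(2/281.6) = 0.927. This part of the objection stands in full.

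A reader might also infer that 1,499 proves a second, hidden alpha of 0.025. The arithmetic is suggestive, but the frame reconstruction fits as well. A and B are defined by follow-up status and C only by baseline status, so it is possible that remaining losses sit mainly in C. On that reading A would receive 352. The article does not settle the matter, and the split of 320, 534 and 646 holds only if the stated counts are the sampling frame.

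Finally, proportional sampling is a legitimate choice. The objectives concern relationships across all subjects, the analysis includes correlation and regression, and the article stresses external validity. A proportional sample is self-weighting for that purpose. *Balanced* may have been meant as representative, but the text does not say so. None of this removes the conflict in the allocation rule or supplies the missing step from 352 to 1,499.

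**Conclusion.** The allocation rule contradicts itself. On the article's own counts proportional sampling gives about 320, 534 and 646, and it cannot be balanced. On the same counts 1,499 does not follow from 352 per group: the two natural routes give 1,650 and about 1,319. The figure of 352 itself matches alpha 0.05/3, while the stated 0.05 gives about 264 to 265.

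The defect lies in the rule and the derivation and does not cost the study its power. Every contrast has at least 93% power for 3 points at the stated alpha, and at least 85% at 0.05/3, against a target of 80%. These figures assume SD 11, 80% response in every stratum and the Study population counts as the frame. The split would change if losses up to 2006 differed between strata.

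**What to change.** State one allocation rule, and say whether the Study population counts are those remaining in 2006; if not, give the 2006 counts.

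- **If proportional:** delete *balanced*. Confine the 352 to the equal-allocation calculation or remove it. Give the A, B and C targets from the 2006 frame (320, 534 and 646 if the stated counts apply). State the alpha used, show how 1,499 was obtained, and report the power of each contrast. This changes text only.
- **If the between-group contrasts have priority:** 500 per activity group, about 83 per centre, is an option. At alpha 0.05/3, power rises from 85.5% to 92.8% for A v B and from 88.0% to 92.8% for A v C, and falls from 96.2% to 92.8% for B v C. Cohort-wide estimates would need weights from the frame counts, and each centre would have to hold enough group A subjects. The sampling fractions would have to change before selection.

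The choice depends on which aim comes first. Either version removes the inconsistency.

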### Variables and measurement instruments

#### Anthropometric measurements

Body weight will be determined on two occasions using a homologated electronic scale (Seca 770) following due calibration (precision ± 0.1 kg), with the patient wearing light clothing and no shoes. These readings will be rounded to 100 g. Height in turn will be measured with a portable system (Seca 222), recording the average of two readings, and with the patient shoeless in the standing position. The values will be rounded to the closest centimetre. Body mass index (BMI)(kg/m^2^) will be calculated. Waist circumference will be measured using a flexible graduated measuring tape with the patient in the standing position without clothing. The upper border of the iliac crests are located, and the tape is wrapped around above this point, parallel to the floor, ensuring that it is adjusted without compressing the skin.

#### Office or clinical blood pressure

Office blood pressure measurement involves three measurements of systolic (SBP) and diastolic blood pressure (DBP), using the average of the last two, with a validated OMRON model M7 sphygmomanometer (Omron Health Care, Kyoto, Japan), by following the recommendations of the European Society of Hypertension[44]. Pulse pressure (PP) will be estimated with the mean values of the second and third measurements.

#### Ambulatory blood pressure monitoring

(ABPM): The ABPM will be performed on a day of standard activity, with a radial tonometer. Radial pulse wave acquisition device (BPro) (HealthSTATS Internaciona. [name]. Singapur. Corea) validated according to the protocol of the European Society of Hypertension (ESH), Association for Advancement of medical Instrumentation (AAMI) and British Hypertension society[45] will be used. The records in which the percentage of valid readings was ≥66% of the total and with valid readings at all times were considered to be valid. Furthermore, for the records to be valuable, at least 14 measurements were required during the daytime period, or at least seven during the night time or rest period. The monitor was scheduled for obtaining blood pressure measurements every 15 min during the daytime and rest period. The average and dispersion estimators of SBP and DBP will be calculated during the 24-h, daytime and night time periods, defined based on the diary reported by the patient. The percentage of blood pressure readings above the reference values was also analysed: 24-h blood pressure greater than 130/80 mmHg, daytime blood pressure greater than 135/85 mmHg and night time blood pressure greater than 120 and 70 mmHg for SBP and DBP, respectively[46]. The patients will be classified according to circadian pattern estimated with the nocturnal fall in SBP and DBP. A dipper pattern was defined as a reduction of 10-20%, extreme dipper if reduction was higher than 20%, non dipper if it was 0-10% and riser if it was below 0% for both SBP and DBP. The patients will be classified too by SBP nigh/day ratio and in Dipper < 0,9, Non Dipper between 0,9 - 1, and Risser > 1.

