### Objectives

1. To analyze the relationship of physical activity and fitness to circadian pattern of blood pressure, central and peripheral blood pressure, PWV, AIx, and carotid intima-media thickness in active and sedentary individuals without arteriosclerotic disease.

2. To analyze the relationship of caloric intake and food pattern to circadian pattern of blood pressure, central and peripheral blood pressure, PWV, AIx and carotid intima-media thickness in active and sedentary individuals without arteriosclerotic disease.

3. To study the correlation of OPG and endoglin levels with arterial stiffness assessed by PWV and AIx, as well as with circadian pattern of blood pressure and carotid intima-media thickness in subjects with different level of physical activity and different nutritional patterns.

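### The ABPM validity rule joins its day and night minimums with 'or', so the seven-reading night minimum never binds, although the dipping classes need both periods

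*Protocol article*

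**What the plan says.** The section on ambulatory blood pressure monitoring sets three conditions for a usable record.

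- The first two are stated together, as a definition of validity: "The records in which the percentage of valid readings was ≥66% of the total and with valid readings at all times were considered to be". That is a 66% share of all readings, plus valid readings at all times. The second condition is not defined.
- The third is added to these: "at least 14 measurements were required during the daytime period, or at least seven during the night time or rest period".

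The schedule is fixed: "The monitor was scheduled for obtaining blood pressure measurements every 15 min during the daytime and rest period". Day and night are not fixed clock periods; the estimators are computed for the 24 h and for the "daytime and night time periods, defined based on the diary reported by the patient".

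Two classifications follow in the same section. One is by dipping: "The patients will be classified according to circadian pattern estimated with the nocturnal fall in SBP and DBP". The other is by ratio: "The patients will be classified too by SBP nigh/day ratio". No separate validity rule is given for either. Circadian pattern is an outcome in all three objectives; the first begins "To analyze the relationship of physical activity and fitness to circadian pattern of blood pressure".

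**The concern.** A nocturnal fall or a night/day ratio can be no more reliable than the weaker of its two means. The protocol has a minimum for each period, but joins them so that meeting one is enough. A record with ample daytime data and very few night readings could then be called dipper, non-dipper or riser. The class limits are close together: cuts at 0%, 10% and 20% are 12.5 mmHg apart at an illustrative day mean of 125 mmHg. A poorly estimated night mean can move a subject across a limit, and so add misclassification to an outcome of every objective.

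The article states this rule itself, so the point is not about detail left to a fuller document.

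**Working it through.** The protocol gives no figure to reproduce here. The check is whether the other two conditions make the 'or' harmless.

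**Inputs from the protocol:** one reading per 15 min, a 66% threshold, and minimums of 14 (day) and 7 (night).

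**Assumptions:** a full 24 h recording; diary nights of 5-10 h (no length is given); within-night SD of 8-10 mmHg; independent readings.

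**Step 1, the 66% rule.** Scheduled readings: 24 × 4 = 96. Needed: 0.66 × 96 = 63.4, so 64.

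**Step 2, is the daytime minimum ever active?** The fewest valid day readings occur when every night slot is valid: 64 − 4 × (night hours). This stays at 14 or more as long as 4 × (night hours) ≤ 50, that is, for nights up to 12.5 h. Every record that meets the 66% rule then satisfies the daytime limb. Under 'or', the third condition is already met and the seven-night minimum has no effect.

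**Step 3, does the 66% rule protect the night?** The fewest valid night readings are 64 − (day slots), or 0 if that is negative. A record with 6 night readings passes if 64 − 6 = 58 day readings are valid.

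| Night (h) | Night / day slots | Fewest valid day | Fewest valid night, 66% rule alone | Share of day slots needed to pass with 6 night readings | Fewest valid night if one per hour is required |
|---|---|---|---|---|---|
| 5 | 20 / 76 | 44 | 0 | 58/76 = 76% | 5 |
| 6 | 24 / 72 | 40 | 0 | 58/72 = 81% | 6 |
| 7 | 28 / 68 | 36 | 0 | 58/68 = 85% | 7 |
| 8 | 32 / 64 | 32 | 0 | 58/64 = 91% | 8 |
| 9 | 36 / 60 | 28 | 4 | 58/60 = 97% | 9 |
| 10 | 40 / 56 | 24 | 8 | not possible (58 > 56) | 10 |

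**Step 4, does the at-all-times condition close the gap?** Taken literally it cannot stand beside a 66% threshold, so it must mean something weaker.

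- Read as one valid reading in each hour, it guarantees seven for nights of 7 h or more, but not for shorter ones. Example: a 6 h night with 72 day and 6 night readings has 78/96 = 81% valid and is accepted.
- Read as some valid reading in each period, an 8 h night could pass with 63 day readings and 1 night reading (64/96).

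**Step 5, precision of the night mean.** SE = SD/√n, at SD 8-10 mmHg:

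- n = 7: 8/√7 to 10/√7 = 3.0-3.8 mmHg
- n = 6: 8/√6 to 10/√6 = 3.3-4.1 mmHg
- n = 5: 8/√5 to 10/√5 = 3.6-4.5 mmHg
- n = 3: 8/√3 to 10/√3 = 4.6-5.8 mmHg

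For scale, a 10% dip from a day mean of 125 mmHg is 12.5 mmHg.

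**The case against.** Three arguments limit the point.

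**The conditions are cumulative.** A record must also have "with valid readings at all times were considered to be valid". If that means one per hour, a record with three night readings fails for any night of 4 h or longer. What remains is nights under 7 h that are one or two readings short, with an SE of 3.3-4.5 instead of 3.0-3.8 mmHg. This stands in full if the hourly meaning is intended, but the text does not say so, and the looser meaning leaves a much wider gap.

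**The 66% rule gives partial protection.** Passing with fewer than seven night readings takes at least 58 valid day readings, which is 91% of the day slots for an 8 h night, and it is impossible for a 10 h night. This also stands. It makes such records less likely without excluding them, least of all for short nights.

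**The 'or' may work period by period:** 14 readings to use the daytime mean, seven to use the night mean. Separate daytime and night estimators are indeed planned, and on this reading the ratio would naturally need both. The reading is possible but not stated. The sentence makes the record as a whole usable on either limb, and nothing restricts the two-period classifications to records that meet both. The 'or' may equally be a slip for 'and'; those who apply the rule will still follow the written word.

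**Conclusion.** The rule as written does not suit the outcome it controls and should be corrected. The result that the seven-night minimum never binds follows from the protocol's own schedule and threshold, for any full 24 h recording with a night up to 12.5 h.

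The size of the harm depends on the undefined at-all-times condition. It is small under an hourly meaning (5-6 readings on 5-6 h nights) and larger under a looser one (down to a single reading on an 8 h night). The affected records are those with 1-6 valid night readings. The SEs rest on the assumed SD of 8-10 mmHg. The protocol gives no distribution of valid night readings, so the number of subjects concerned cannot be computed.

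A reader might go further in two ways that the document does not support. One is that subjects with no night data would be classified, or that classes would be assigned on noise in general. A record without night readings yields no ratio, and with 5-6 readings the loss of precision against seven is modest. The other is that night readings are lost selectively, for example because poor sleepers remove the device. Nothing in the protocol bears on that.

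**What to change.** For any record used for nocturnal fall or the night/day ratio, require at least 14 valid daytime **and** at least 7 valid night readings. These are the protocol's own numbers; by Step 2, only the night minimum will exclude anyone.

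Replace the at-all-times wording with a rule that can be counted, for example at least one valid reading in each hour. The two changes work together: the hourly rule secures nights of 7 h or more, and the minimum of seven covers shorter ones.

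Records adequate in one period only may still contribute that period's means; the hourly rule should then be applied within that period.

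The cost is one word and one clause, plus the loss of some records from the circadian analysis. That loss is probably small, because a record short of night readings needs at least 58 valid day readings to be accepted at present, but the document does not allow a count.

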#### Central blood pressure and augmentation index

Central blood pressure will be measured with Pulse Wave Application Software (A-Pulse) (HealthSTATS International, [name]. Singapore, Korea) using tonometry to capture the radial pulse and by equation patented estimate central blood pressure. The increase in central blood pressure, mean blood pressure and radial Augmentation index will be estimated. Radial AI will be calculated as follows: (Second peak systolic blood pressure [SBP2] - diastolic blood pressure [DBP])/(first peak SBP - DBP) × 100 (%).

It is the same instrument that performs the 24 ABPM (BPro), with an specific software to determine the central blood pressure and estimation of the parameters derived from it.

#### Pulse wave analysis (PWA) and pulse wave velocity (PWV)

In the Salamanca cohort, AIx and PWV will also be estimated using the SphymgoCor System (AtCor Medical Pty Ltd Head Office, West Ryde, Australia), currently the gold standard for measuring arterial stiffness[1], and will serve as a quality control for the measurements obtained with the Pulse Wave Application Software (A-Pulse). Using the SphygmoCor System (Px Pulse Wave Analysis), with the patient in the sitting position and resting the arm on a rigid surface, pulse wave analysis will be made with a sensor in the radial artery, using mathematical transformation to estimate the aortic pulse wave. From the morphology of the aortic wave, central (aortic) blood pressure, central ventricular load, diastolic perfusion pressure, subendocardial viability index, the pressure increase, central pressure pulse and Central AIx will be estimated. Central AIx, will be estimated using the following formula: Increase in central pressure * 100/Pulse pressure. Using the SphygmoCor System (Vx Pulse Wave Velocity), and with the patient in the supine position, the pulse wave of the carotid and femoral arteries will be analyzed, estimating the delay with respect to the ECG wave and calculating the PWV. Distance measurements will be taken with a measuring tape from the sternal notch to the carotid and femoral arteries at the sensor location.

